#### Spatial Memory

Spatial memory is strongly influenced by vestibular inputs [35,48] and will be assessed using the triangle completion task and the 4 Mountains Test. The triangle completion task combines vestibular and somatosensory inputs and interacts with cognitive and motor processes to perceive self-motion and generate a cognitive map of space [49-51]. The 4 Mountains Test uses a delayed match-to-sample paradigm on a computer-based image [52]. This is a highly sensitive test in older adults with mild cognitive impairment and can be easily applied in routine clinical practice [53].

####  Qualitative Assessment

A qualitative assessment in the form of a semistructured interview designed to investigate the acceptability of the treatment will occur at week 10 for selected noisy galvanic vestibular stimulation and sham participants. We aim to interview 5-6 participants in the noisy galvanic vestibular stimulation intervention group with a sample purposively selected to represent variation in intervention compliance and response; 2 sham participants will also be interviewed to explore the acceptability of the trial process. Physiotherapists delivering the intervention will be interviewed to explore the study processes, acceptability, and value of the intervention from their perspective. Semistructured interviews will be transcribed verbatim and uploaded to NVivo. We will conduct thematic analysis of the data using the 6-stage process of analysis (transcription, reading and familiarization, coding, searching for themes, reviewing themes, defining and naming themes, and finalizing the analysis) by Braun and Clarke [54]. Data will be initially analyzed at a semantic level to draw on the reflections of participants in relation to processes and practical aspects of the assessments and interventions. However, researchers will also identify latent themes, such as underlying ideas and assumptions, which are theorized to shape and inform semantic data.

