
### Objectives

This study aims to assess the feasibility of a future definitive randomized trial examining the effect of balance rehabilitation augmented with noisy galvanic vestibular stimulation in older adults at risk of falls. The primary objective is to assess the feasibility of the study process, including (1) rate of participant recruitment, conversion, and retention; (2) feasibility of screening processes; (3) utility of data collection and outcome measures; and (4) acceptability and suitability of the intervention and study procedures.

Our secondary objectives are to (1) evaluate participant opinions of the intervention as a basis for refinement of the definitive trial; (2) select a responsive and meaningful outcome measure; and (3) to inform the power and sample size calculations for the future full randomized controlled trial.

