## Methods

### Trial Design

This study is a 3-armed randomized controlled trial design with a qualitative component. A total of 72 participants will be randomly allocated in a 1:1:1 ratio to a noisy galvanic vestibular stimulation group, sham group, or no intervention control group. Recruitment will close once 24 participants have been recruited into the noisy galvanic vestibular stimulation arm. Outcome assessment will occur at baseline (week 1), posttreatment (week 10) and at the 3-month follow-up posttreatment (Table 1).

**Table 1 table1:** Standard Protocol Items-Recommendations for Interventional Trials tabulation of study enrollment, interventions, and assessments.

Study events		Study period						
		Enrollment	Postallocation					Closeout
			Week 1	Week 2-9	Week 10	Week 22		

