### Intervention

The balance retraining program focuses on exercises and activities that stimulate the vestibular system and the integration of all sensory inputs for effective postural control (Table 2) [7,45,47]. The exercises are delivered in a group setting of up to 6 participants with difficulty in the exercises being individualized for each participant. The balance retraining program is delivered by an experienced and registered physiotherapist with 1 assistant for groups of 4 and above. Participants in the noisy galvanic vestibular stimulation group will receive 30 minutes of white noise galvanic vestibular stimulation during the exercise program; the sham group will receive sham stimulation during the exercise program, and the control group will receive no intervention [4,21]. The noisy galvanic vestibular stimulation generates a 0 mean random signal with equal intensities at different frequencies via electrodes applied over the mastoid process, which are attached to a noisy galvanic vestibular stimulation device (Galvanic Stimulator 0811, Soterix Medical). The intensity is set at 0.5 mA and is of imperceptible magnitude.

The noisy galvanic vestibular stimulation and sham groups will commence the exercise program within 10 days of the initial assessment. The exercise group will be offered to the control group after the 3-month follow-up assessment at the end of their participation in the study (Figure 1).

**Table 2 table2:** Summary of the multisensory balance program.

Category	Time (minutes)	Examples of exercises
Warmup	5	Multidirectional walking, turning, changing speed and size of movement
Vestibular	10	Standing, head turns with a target- fixed- gaze stimulating the vestibular ocular reflex. Standing on unstable surfaces eyes closed
Vision	5	Eyes open walking on narrow beam and standing on unstable surfaces
Somatosensory	5	Testing individuals’ limits of stability; multidirectional lean, standing on unstable surfaces
Mobility-center of gravity control	5	Walking a straight line, weaving and turning during gait, changing base of support and posture simultaneously while moving from low to high surfaces
Aerobic	5	Exercycle

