### Threats to Attainment of Study Goals

#### Overview

As a feasibility study investigating a novel treatment, there are a number of aspects of the study that could impact both the attainment of study goals and progression to a fully powered study. Possible threats identified by the study team are the inability to recruit, poor tolerance for noisy galvanic vestibular stimulation, technical issues with noisy galvanic vestibular stimulation, and adverse reactions to noisy galvanic vestibular stimulation. Although there have been very low rates of adverse effects with noisy galvanic vestibular stimulation, the participants in this study receive a larger cumulative dose of noisy galvanic vestibular stimulation compared with previous studies.

The trial will be deemed a success based on the following: (1) recruitment at a rate of 2 participants per week; (2) participants attending 75% of available exercise sessions over 8 weeks; (3) achieving 80% data completeness at each time point; (4) report of no serious adverse events related to the intervention; and (5) a subjective sense of perceived benefit, enjoyment, and engagement in the program present in participants who underwent qualitative assessment.

On the basis of previous research, we estimate that a sample of 72 would be sufficient to investigate feasibility and to determine the sensitivity of our outcome measures to inform sample size calculation for the full study.

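### No control participant is interviewed, and the 80% data-completeness criterion has no per-arm threshold, so the deferred-exercise control arm is weakly tested for feasibility

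*Protocol article*

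**What the plan says.** **Objectives.** The first primary objective includes "rate of participant recruitment, conversion, and retention", with no arm singled out. The fourth covers acceptability and suitability of the study procedures as well as of the intervention.

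**Design (Trial Design).** "A total of 72 participants will be randomly allocated in a 1:1:1 ratio", and "Recruitment will close once 24 participants have been recruited into the noisy galvanic vestibular stimulation arm". All arms are assessed at week 1, week 10 and the 3-month follow-up (the week 22 column of Table 1).

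**Control arm (Intervention).** "The exercise group will be offered to the control group after the 3-month follow-up assessment at the end of their participation in the study".

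**Interviews (Qualitative Assessment).** The interview "will occur at week 10 for selected noisy galvanic vestibular stimulation and sham participants". The planned sample is 5-6 nGVS participants and 2 sham participants, the latter specifically to explore the trial process. Treating physiotherapists are also interviewed. Table 1 shows interviews at week 10 only.

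**Success rule (Threats to Attainment of Study Goals, Overview).** There are five criteria: recruitment of 2 per week; 75% session attendance; "3) achieving 80% data completeness at each time point"; no intervention-related serious adverse events; and perceived benefit among interviewees. Table 3 (participant adherence row) puts the completeness figure at 95% instead of 80%.

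**The concern.** A feasibility study with a no-treatment arm should show whether people will accept that allocation and stay for follow-up. Controls here learn their allocation after the baseline assessment and have no access to the programme until about 21 weeks later (week 1 to week 22).

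Two parts of the plan bear on this, and both are weak for controls. The interviews leave them out, although the acceptability objective extends to study procedures. The success criteria contain no retention test specific to them. A poorly tolerated control condition could therefore go unexplained, and the study could still meet its stated criteria. The definitive trial might then adopt a comparator prone to differential loss, which biases between-arm comparisons and cannot be cured by a larger sample.

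**Working it through.** **Step 1. Which success criteria reach controls?**

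| Criterion | Bears on keeping controls in the study? |
|---|---|
| Recruitment, 2 per week | No. It concerns entry, not staying |
| 75% of sessions attended | No. Controls have no sessions before week 22 |
| 80% data completeness at each time point | Yes, but no threshold by arm |
| No intervention-related serious adverse events | No. Controls have not received the intervention |
| Perceived benefit among interviewees | No. No control is interviewed |

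**Step 2. Interviews.** Participants interviewed: 5-6 nGVS + 2 sham = 7-8; controls 0. Sham participants attend the full exercise programme, so they can speak about assessments and attendance but not about being allocated to nothing. At week 10 the follow-up interval has not yet happened for anyone interviewed.

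**Step 3. Plan's own figure.** 3 arms × 24 = 72, so controls are 24/72 = one third. This agrees with Trial Design. Exact arm sizes may differ slightly, because allocation is by minimisation and recruitment closes on the nGVS count.

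**Step 4. What a pooled criterion allows.** Assume that completeness means participants assessed and that the denominator is all 72. Participants needed = threshold × 72, rounded up. Minimum controls = needed − treated participants assessed (maximum 48).

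| Threshold | Needed | Treated assessed | Minimum controls | Controls that may be lost |
|---|---|---|---|---|
| 80% | 57.6 → 58 (80.6%) | 48/48 | 10 | 14 of 24 (58%) |
| 80% | 58 | 46/48 | 12 | 12 of 24 (50%) |
| 80% | 58 | 44/48 | 14 | 10 of 24 (42%) |
| 95% | 68.4 → 69 (95.8%) | 48/48 | 21 | 3 of 24 (12.5%) |
| 95% | 69 | 46/48 | 23 | 1 of 24 (4%) |

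At 95% with 44/48 treated assessed, even full control data fail: 68/72 = 94.4%.

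**Step 5. What a per-arm 80% criterion would require.** 0.80 × 24 = 19.2, so 20 of 24 (83.3%), allowing 4 losses per arm.

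**Step 6. Chance of passing (exact binomial, independent participants).** The completion rates are assumptions; the article gives none. The range in the middle column is for 90% to 95% true completion in the treated arms.

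| True control completion | Pooled rule (≥58/72) | Control-arm rule (≥20/24) |
|---|---|---|
| 60% | 0.52 to 0.81 | 0.013 |
| 70% | 0.80 to 0.96 | 0.11 |

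**Step 7. Price of the per-arm rule.** If true completion is 90% in every arm, each arm passes with probability 0.915 and all three with 0.915³ = 0.77; the pooled rule passes with probability 0.995. At 95% in every arm, the per-arm figure is 0.994³ = 0.98.

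**The case against.** **Retention is recorded.** A reader might infer that control retention goes unanswered. The article does not support that. Controls are assessed at weeks 10 and 22, study completion is counted under Recruitment, and completion of follow-up sessions is collected in Table 3, all without excluding an arm. Loss of 14 controls would be visible in those data whatever the success rule said. This stands; the gap is in the criterion, not in the data.

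**Pooling is an inference.** The article says neither pooled nor by arm, and a condensed article may leave tabulation to the full protocol. This also stands, so Step 4 is conditional. Even so, the article fixes its success criteria, and a threshold that can be read in ways with such different consequences is worth settling.

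**The 14 of 24 figure is an extreme.** It needs no loss among 48 treated participants, and partly missing records among attenders would use up some of the 20% allowance. That is fair, and 10 of 24 is the figure at 44/48. Under the 95% figure, most of the masking disappears.

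**Controls may not be the arm that drops out most.** Treated participants carry twice-weekly sessions for 8 weeks. Controls have the later offer of exercise, travel vouchers, flexible scheduling and a contact number. The article gives no dropout figure for any arm. Higher control loss is plausible, not documented.

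**The interviews are mainly about the treatment.** Qualitative Assessment does give treatment acceptability as their purpose, and sham interviewees will already have completed the same test battery twice. That explains the sample only in part: the sham interviews are aimed at the trial process, and that group does not experience the control condition.

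**Conclusion.** The point holds in two parts of unequal firmness.

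The interview gap is plain from the text: 0 of 7-8 participants interviewed are controls, and all interviews precede the follow-up interval. Acceptability of a no-treatment allocation with exercise deferred past week 22 is therefore never elicited, although it falls within a primary objective.

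The completeness gap is conditional. With 24 per arm, pooling, and completeness read as participants assessed, the 80% criterion tolerates the loss of 10 to 14 of 24 controls when 44 to 48 of the 48 treated participants are assessed. Under the Table 3 figure it tolerates at most 3. The unresolved conflict between 80% and 95% thus decides whether substantial control attrition would register as a failure.

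Neither part invalidates the study. Both limit what its success rule can say about one third of those randomised.

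**What to change.** 1. Reconcile the 80% in the success criteria with the 95% in Table 3, and say whether completeness counts participants assessed or data items.
2. Apply the criterion to each arm separately at weeks 10 and 22, with randomised participants as the denominator, and report it by arm. At 80% this means at least 20 of 24; at 95%, 0.95 × 24 = 22.8, so 23 of 24.
3. Add interviews with 2-3 controls, including any who withdrew and are willing, covering the allocation, the wait and the assessments. Hold them at or after their week 22 assessment and have the existing interview team run them, so that the assessor's blind is unaffected.

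Cost: rewording one criterion and a few more interviews and transcripts. The per-arm criterion is harder to meet. With only 24 per arm it can fail by chance when retention is good (Step 7), so a narrow miss in one arm should prompt a look at the reasons for loss.

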### Intervention

The balance retraining program focuses on exercises and activities that stimulate the vestibular system and the integration of all sensory inputs for effective postural control (Table 2) [7,45,47]. The exercises are delivered in a group setting of up to 6 participants with difficulty in the exercises being individualized for each participant. The balance retraining program is delivered by an experienced and registered physiotherapist with 1 assistant for groups of 4 and above. Participants in the noisy galvanic vestibular stimulation group will receive 30 minutes of white noise galvanic vestibular stimulation during the exercise program; the sham group will receive sham stimulation during the exercise program, and the control group will receive no intervention [4,21]. The noisy galvanic vestibular stimulation generates a 0 mean random signal with equal intensities at different frequencies via electrodes applied over the mastoid process, which are attached to a noisy galvanic vestibular stimulation device (Galvanic Stimulator 0811, Soterix Medical). The intensity is set at 0.5 mA and is of imperceptible magnitude.

The noisy galvanic vestibular stimulation and sham groups will commence the exercise program within 10 days of the initial assessment. The exercise group will be offered to the control group after the 3-month follow-up assessment at the end of their participation in the study (Figure 1).

**Table 2 table2:** Summary of the multisensory balance program.

Category	Time (minutes)	Examples of exercises
Warmup	5	Multidirectional walking, turning, changing speed and size of movement
Vestibular	10	Standing, head turns with a target- fixed- gaze stimulating the vestibular ocular reflex. Standing on unstable surfaces eyes closed
Vision	5	Eyes open walking on narrow beam and standing on unstable surfaces
Somatosensory	5	Testing individuals’ limits of stability; multidirectional lean, standing on unstable surfaces
Mobility-center of gravity control	5	Walking a straight line, weaving and turning during gait, changing base of support and posture simultaneously while moving from low to high surfaces
Aerobic	5	Exercycle

**Figure 1 figure1:**
[figure not shown]
Participant flow through the study. nGVS: noisy galvanic vestibular stimulation.

### Data Management

Data will be entered directly into customized REDCap digital data collection forms; any paper forms will be uploaded into the REDCap data management system. REDCap access is password-protected and requires dual identification for entry. Forms will have internal checks for completeness and where appropriate individual criteria will have automatic range checks. All data will be deidentified on exportation from the database with analyses performed by a blinded member of the research team. Blinding will not be lifted until data collection and final follow-up assessment has been completed. Data will only be accessible to the research team. The results will be made available to participants on request and will be published in a peer-reviewed journal.

### Statistical Methods

The analysis will focus on univariate models, such as linear mixed models, but include measures of association. An examination of within-subject data will be carried out to measure changes in key outcomes. This will help refine participant selection, protocol, and suitability of outcome measures for the full study. Responsiveness metrics such as effect size and standardized response mean will be calculated for postural control outcomes to inform the selection of the primary outcome and power calculations for the intervention study.

Semistructured interviews will be transcribed verbatim and uploaded to NVivo. Data will undergo thematic analysis using the Braun and Clark six-stage process of analysis (transcription, reading and familiarization, coding, searching for themes, reviewing themes, defining and naming themes, and finalizing the analysis) [54]. Data will be initially analyzed at a semantic level to draw on the reflections of participants in relation to processes and practical aspects of the assessments and interventions. However, researchers will also aim to identify latent themes—the underlying ideas and assumptions that are theorized to shape and inform semantic data.

### Threats to Attainment of Study Goals

#### Overview

As a feasibility study investigating a novel treatment, there are a number of aspects of the study that could impact both the attainment of study goals and progression to a fully powered study. Possible threats identified by the study team are the inability to recruit, poor tolerance for noisy galvanic vestibular stimulation, technical issues with noisy galvanic vestibular stimulation, and adverse reactions to noisy galvanic vestibular stimulation. Although there have been very low rates of adverse effects with noisy galvanic vestibular stimulation, the participants in this study receive a larger cumulative dose of noisy galvanic vestibular stimulation compared with previous studies.

The trial will be deemed a success based on the following: (1) recruitment at a rate of 2 participants per week; (2) participants attending 75% of available exercise sessions over 8 weeks; (3) achieving 80% data completeness at each time point; (4) report of no serious adverse events related to the intervention; and (5) a subjective sense of perceived benefit, enjoyment, and engagement in the program present in participants who underwent qualitative assessment.

On the basis of previous research, we estimate that a sample of 72 would be sufficient to investigate feasibility and to determine the sensitivity of our outcome measures to inform sample size calculation for the full study.

**Staff training**			
	Training	Protocols are standardized and training involves didactic teaching, role playing and modeling	Protocol read and training modules completed by all treating physiotherapists
	Supervision	Frequency and duration of supervision are set out	Therapists are supervised in their initial treatment sessions and then have “spot checks” for compliance with the exercise program, progressions and documentation. All therapists have a contact number of the PI^a^ and project manager in the case of an adverse event or self-identified queries or supervision requirements
	Measurements	Establishing compliance with delivery of treatment	Treatments recorded on a customized, standardized form. Checked by the project manager to ensure data completeness
**Recruitment**			
	Methods	Staged approach to advertising	Data collected regarding methods of recruitment and number of people who responded via each method, response rate, number of responders sent a participant information sheet after initial contact
	Eligibility	Number of responders who were eligible and consented to the study. Reasons for ineligibility or deciding not to consent	Screening data recorded on a standardized form Average recruitment over the study of 2 participants per week
**Intervention delivery **			
	Intervention differences	Dose of exercise and noisy galvanic vestibular stimulation intervention	Expected dose and core components of the program as per the intervention protocol were recorded on the standardized program record
	Therapist competence	Experience and competence	Years of experience and areas of practice recorded for all treating therapists
	Monitoring drift	Ensure program delivered correctly throughout the program	Physiotherapists completed and returned a standardized record of all treatment visits. One visit per program between week 6 and 8 by a PI or project manager to ensure program continues to be delivered correctly
	Corrective feedback	Feedback procedures in place	Ongoing support and mentoring available if discrepancies noted during monitoring of treatment programs and documentation
